#### Control group

Participants in the control group will not receive the STAK-D intervention, but will continue with usual clinical care according to that available at the site from which they were recruited. Both participating sites operate under the same general standardisation of care; they both adhere to Global IDF/ISPAD Clinical Practice Consensus Guidelines [41], NICE guidelines for clinical care of diabetes in children and young people [42], and the UK National Health Service (NHS) national diabetes best practice tariff, which specifies requirements for the service. Quantifying usual care with regards physical activity is difficult, although our previous qualitative research suggests that lifestyle physical activity advice is limited in the current clinical care of children with T1DM [18, 24]. Usual care at each site will be described as part of this feasibility study following recommendations by Erlen et al. [43]; this will allow for accurate definition of usual care in future trial design.

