#### Primary outcome measures

The primary outcome measures for the feasibility study are as follows:Recruitment rateAn estimate of the number of eligible patients and likely uptake rate will be assessed. The response rate for mailed invitation will be compared to clinic (face-to-face) recruitment rates. Refusal rate and reasons for nonparticipation will be assessed. This will enable a prediction of recruitment rate, number of sites and length of time needed to recruit the required number of patients for a future trial. A recruitment rate of between 25 and 40% would be considered reasonable based on our previous research [22] and similar studies [44, 45]Adherence ratePattern of intervention use will be monitored to assess fidelity of intervention delivery. We will explore users’ activity by website and page visits, more or less commonly used elements, and engagement with goal-setting and activity tracking. We will assess user satisfaction with STAK-D (e.g. navigation, ease of use, technical issues) at 6 months. Acceptable compliance will be defined as the child using the online resources and tracking their daily activity (using the PolarActive watch). Noncompliance will be defined as the child’s failure to access the STAK-D website and track their physical activity over the intervention periodRetention rateRetention will be defined as the number of participants completing the STAK-D programme including all scheduled follow-up data collection (T0, T1 and T2) compared to the number started. A retention rate of at least 70% at each time point would be considered feasible based on our previous research [22] and similar studies [44, 45]Data completion rateCompletion of outcome measures will be recorded at T0, T1 and T2 (complete and partial or noncompletion with reasons, including time to complete). Measures will be determined acceptable to parents and children (in terms of literacy, cognitive ability and capacity to understand) if more than 70% are fully completed (indicating quality data), and reported participant burden is minimal.The feasibility of gathering routinely collected clinic data from patients’ electronic diabetes record (height, weight, HbA1c level and insulin dosage) at T0, T1 and T2 will be assessed. This will allow us to ascertain the proportion of our sample with complete clinical records, and whether records will be accessible to our researchers at specified data collection time points. Feasibility of collecting observational data in this way will be determined if more than 85% of the sample have complete clinical records availableAdverse eventsAny adverse events experienced as a result of participation in the intervention will be recorded and evaluated. Adverse events are defined as any serious negative outcome resulting from the physical activity undertaken as part of the STAK-D programme. Severe hypoglycaemia, i.e., a blood glucose level below 4 mmol/l requiring the help of another person to treat it, will be considered an adverse event in either group. Data from meter and pump downloads combined (and meter downloads alone for those patients not on insulin pump therapy) will be used for identification of hypoglycaemic episodes, as per usual care at our participating sites. To determine the likelihood of adverse events being associated with the physical activity undertaken as part of the STAK-D programme, we will record whether the frequency and/or severity of hypoglycaemic episodes increased during the intervention period. The occurrence of adverse events related to the intervention will be assessed and compared to the control group (see ‘Harms’ section for potential adverse events).

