### Sample size

The sample size will be adequate to estimate the critical parameters (e.g. recruitment rate) to the necessary degree of precision and to provide key information on the feasibility of the intervention. There are approximately 170 patients in the specified age range across both recruitment sites, prior to exclusions. We will target the recruitment of 50 child-parent dyads (approximately five per month over 9–10 months). We envisage this to be achievable since previous studies indicate a 40–50% response rate with similar populations [22, 55] and our selected feasibility study sites currently have recruitment rates exceeding 100% for NIHR-adopted studies. Recruitment of a minimum of 33 child-parent dyads (40%) would be deemed necessary to progress to full trial; should recruitment be problematic a remedial act will be to revise inclusion criteria to include age range 8–13 years. At T2, up to 25 child-parent dyads and up to 10 HCPs will take part in interviews.

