### Assignment of interventions

#### Sequence generation

Consented participants will be individually randomised with a 1:1 allocation to receive either the intervention or usual care; no participant will receive less than standard care. The allocated treatment will be determined using the ‘Sealed Envelope Company’ randomisation service [56]. After receiving consent and assent, and collection of baseline data, the researcher will send an SMS text message to the ‘Sealed Envelope Company’, which will automatically randomise the participant to the intervention or control group.

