##### Harms

A side effect of physical activity for people with T1DM is changes in blood glucose levels, above or below normal, causing unfavourable symptoms. Hypoglycaemia is when blood glucose levels drop too low and hyperglycaemia is where blood glucose levels spike too high. The hypoglycaemic and hyperglycaemic risks in this research are no more severe than expected for the participant’s condition (e.g. as a side effect of insulin treatment). Furthermore, the physical activity encouraged through this intervention is not of a high enough intensity or a long enough duration to be deemed dangerous or high-risk to children (the proposed modifications to physical activity levels are in accordance with published guidelines for paediatric T1DM [42]). However, if there is considerable exacerbation (increase in occurrences or severity compared to before participation in the intervention) of episodes of hypoglycaemia and/or hyperglycaemia (blood glucose >14 mmol/l), then the participant will be asked to discontinue their use of the intervention, re-establish their previous daily routine and seek medical advice.

Adverse events will be classified on the basis of severe hypoglycaemia or hyperglycaemia, or any other injury or incident believed to be caused by participation in the STAK-D intervention. All information pertaining to adverse events noted by the researcher during the study will be listed by subject, detailing the episode date and time of onset and date and time of resolution. The onset of adverse events will be shown relative (in number of min/h/days) to the time of the highest bout of physical activity.

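### Read literally, the retention rule can never count a control dyad as retained; it should count follow-up data over all randomised, whatever the programme use

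*Protocol article*

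**What the plan says.** Under Primary outcome measures, the protocol article defines retention as "the number of participants completing the STAK-D programme including all scheduled follow-up data collection (T0, T1 and T2) compared to the number started". The threshold follows directly: "A retention rate of at least 70% at each time point would be considered feasible". The same section lists adherence, meaning use of the website and activity tracking, as a separate primary outcome.

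The Control group section states: "Participants in the control group will not receive the STAK-D intervention". Sequence generation gives the allocation: "Consented participants will be individually randomised with a 1:1 allocation to receive either the intervention or usual care". The Sample size section sets a target of 50 dyads and a minimum of 33.

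The Aim section makes being able to retain patients one of the conditions for calling a definitive trial feasible. Control children are assessed on the same schedule as intervention children: the objective physical activity measure is taken in both groups at T0, T1 and T2. The article gives no other definition of retention, either for the control arm or for the trial as a whole.

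**The concern.** In a two-arm trial, retention should measure how many of those randomised are still giving data, in both arms. The rule here asks for completion of a programme that one arm is never offered. An analyst who follows the words has two choices, and neither answers the question. Counting everyone makes the threshold unreachable. Counting only those who started STAK-D leaves the control arm out.

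Two further problems sit in the same sentence. It joins programme completion to follow-up, although programme use already has its own outcome, and the article does not say what completing the programme means. It also asks for T0, T1 and T2 together, while the threshold is to be judged at each of them.

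What is at stake is the attrition figure carried into the definitive trial. That trial's sample size needs losses from both arms. Participants are not blinded, so losses could differ between the arms.

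**Working it through.** The 70% threshold was set by reference to earlier studies, so there is no calculation to reproduce. The check is what values the stated rule can take.

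**Inputs.** Target of 50 dyads and minimum of 33 (Sample size); 1:1 allocation (Sequence generation); no STAK-D for controls (Control group); threshold of 70% (Primary outcome measures). I assume an even split: 25 per arm at the target, and 16 or 17 in the intervention arm at the minimum.

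**Reading A: programme completers over all randomised.** The maximum equals intervention dyads ÷ all dyads, reached with no loss at all.
- Target: 25/50 = 50%.
- Minimum: 16/33 = 48% or 17/33 = 52%.

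All are below 70%. Passing would need 0.70 × 50 = 35 of the 50 dyads to be in the intervention arm, which chance imbalance under 1:1 allocation would not plausibly give.

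**Reading B: programme completers over STAK-D starters only.** With all 25 intervention dyads starting, 0.70 × 25 = 17.5, so 18 are needed. 18/25 = 72% (exact 95% CI 51% to 88%). Control follow-up does not enter. The control counts below are illustrative:

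| Intervention followed | Control followed | Rule gives | Whole-trial retention |
|---|---|---|---|
| 18/25 | 20/25 | 72%, pass | 38/50 = 76% |
| 18/25 | 10/25 | 72%, pass | 28/50 = 56% |
| 18/25 | 5/25 | 72%, pass | 23/50 = 46% |

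**Reading C: the programme taken to mean study participation.** Controls count and full follow-up gives 50/50 = 100%. The threshold needs 35/50 = 70% (exact 95% CI 55% to 82%). At the minimum, 0.70 × 33 = 23.1, so 24/33 = 73% is needed.

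**All visits against each visit.** Suppose exactly 35 of 50 dyads give data at T1 and 35 of 50 at T2, so the threshold is just met at both. The number with both lies between 35 + 35 − 50 = 20 (40%) and 35 (70%). It is 70% only if the same dyads are missing both times. An all-visits count is a single figure and cannot be compared with a separate threshold at T1 and at T2.

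**The case against.** The best defence is Reading C. The definition lists data collection as part of what is completed, and it includes T0. Under Recruitment and Sequence generation, baseline data are collected before randomisation, so T0 cannot belong to the intervention. The Aim section also speaks of retention at trial level. This reading is plausible, and the authors would be unlikely to score every control dyad as lost. Against it, the Interventions section and its Table 1 describe the programme as the intervention, and Study design contrasts it with usual care. The wording is therefore ambiguous at best.

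Several stronger inferences are tempting, but the documents do not support them.
- *The trial cannot see control drop-out.* Completion of measures is recorded at T0, T1 and T2 without restriction by arm, with reasons for noncompletion. Missing data are to be quantified, and participants who drop out are approached for interview. The information will exist; only the retention rule leaves it out.
- *A child who stops the programme counts as lost.* The Harms section says that, after a considerable exacerbation, "then the participant will be asked to discontinue their use of the intervention". It does not end follow-up or classify the child. Completion is not defined by website use either, so the classification is unclear rather than stated.
- *Dyads who never start are dropped from the denominator.* Consent, baseline and randomisation take place at one meeting, so starting may be close to being randomised. The text does not settle it.
- *Failing 70% stops the definitive trial.* The only numerical criterion worded as a requirement is on recruitment: "Recruitment of a minimum of 33 child-parent dyads (40%) would be deemed necessary to progress to full trial". The retention figure is one that would be considered feasible, and the rates are reported descriptively.

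A statistical analysis plan is promised and is not shown; it may settle these points. That does not remove the concern, because the article states a rule and a threshold, and the analysis plan would have to depart from that rule to be right.

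**Conclusion.** The retention definition is wrong as written for a two-arm trial. Taken literally, it caps retention at about 50% with perfect follow-up, or it ignores half the trial. The 50% rests on an even split of 50 dyads (48% to 52% at the minimum of 33). The whole-trial figures of 46% to 76% under Reading B rest on illustrative control counts: they show what the rule would miss and do not predict a result.

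The authors probably did not intend the literal rule, and nothing here shows that the feasibility decision will fail or that control losses will go unrecorded. Even under the generous reading, the overlap with adherence and the mismatch between an all-visits count and a per-visit threshold remain. Severity is moderate: this is a primary feasibility outcome with a threshold attached, but correct retention can be computed from data already being collected in both arms.

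**What to change.** Define retention as the number of dyads giving outcome data at T1, and separately at T2, divided by all dyads randomised, whether or not they used or finished the programme. Apply the 70% threshold to the whole trial at each of the two time points and report the figures by arm beside it. Move programme completion to the adherence outcome. A child who stops using the programme but gives data then counts as retained.

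Under this rule perfect follow-up gives 50/50 = 100%, and the threshold is met with 35 of 50, or 24 of 33 at the minimum recruitment. Only wording changes; no visit or measurement is added. The downside is that the figure may be slightly less favourable if dyads who never start enter the denominator. Settle the definition before retention results are seen, since recruitment was already under way when the article was revised.

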STAK-D is a complex intervention which has been designed for implementation as an adjunct to clinical care in T1DM management. It is targeted at children aged 9–12 years and their families. Targeting this age range is appropriate since participants are likely to have a level of independence commensurate with using computer-based packages at home (98%) [37] with support from their parents. Also, intervention is beneficial at this age since lifestyle behaviours which are adopted preadolescence are more likely to be sustainable and, therefore, to influence disease risk factors across the life course [38].

The STAK-D programme combines educational (information, physical activity guidance, safety information), behavioural (physical activities and activity tracking) and cognitive-behavioural (physical activity monitoring and goal-setting) strategies to promote children’s self-efficacy for physical activity. STAK-D draws upon social cognitive theory constructs of self-efficacy and observational learning [39]. The intervention targets children who have barriers to physical activity and aims to promote self-efficacy via observing role models, mastery experience and persuasion (via education). It provides general advice around regular blood glucose monitoring (e.g. before, during and after physical activities and regularly throughout the day) and healthy eating, which has been approved by diabetes specialists, but it does not give guidance on insulin dosage and administration or carbohydrate counting. For this, families are encouraged to contact their clinical team, either using the ‘Ask the Expert’ element of the website or at their standard clinic appointments.

In addition to the website, STAK-D utilises a wrist-worn activity monitor (PolarActive; Polar Electro Inc., Lake Success, NY, USA) to encourage activity monitoring and goal-setting behaviours. The site is password-protected and can currently only be accessed by research participants and personnel.

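### Injuries and other incidents count as adverse events only if attributed to STAK-D, so the planned comparison with control is not like with like

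*Protocol article*

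**What the plan says.** Adverse events are one of the primary outcomes in the protocol article, and the fifth of its main objectives is to examine potential adverse effects.

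The Primary outcome measures section gives the definition: "Adverse events are defined as any serious negative outcome resulting from the physical activity undertaken as part of the STAK-D programme". It makes one exception. Severe hypoglycaemia (glucose under 4 mmol/l with someone else's assistance needed) "will be considered an adverse event in either group". It then plans a comparison between arms: "The occurrence of adverse events related to the intervention will be assessed and compared to the control group".

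The Harms section classifies events as severe hypoglycaemia or hyperglycaemia, or "any other injury or incident believed to be caused by participation in the STAK-D intervention". It lists the events that the researcher notes.

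On finding low-glucose episodes, the Primary outcome measures section says: "Data from meter and pump downloads combined (and meter downloads alone for those patients not on insulin pump therapy) will be used for identification". To judge whether events are associated with STAK-D activity, "we will record whether the frequency and/or severity of hypoglycaemic episodes increased during the intervention period". The Background says of STAK-D: "It provides general advice around regular blood glucose monitoring (e.g. before, during and after physical activities and regularly throughout the day".

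The Control group section states that control families do not receive STAK-D. The Blinding section states that the researchers who deliver the intervention cannot be blinded and that the follow-up assessor may not be.

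**The concern.** A comparison between randomised arms is informative about harm only if an event of the same kind is counted in the same way in both. Here a child's injury enters the count only once someone has decided that STAK-D caused it. No control child can meet that condition, so the background rate of injuries and incidents in active 9–12-year-olds is never observed. Whatever is recorded in the intervention arm will stand beside a control figure of zero that carries no information.

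The order of steps adds to this. Attribution comes before recording and is made by staff who know the allocation. If they attribute readily, STAK-D looks harmful; if they attribute reluctantly, real harms go unlisted. Neither error can be put right at analysis, because unattributed events in either arm are not in the data.

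Hypoglycaemia raises a separate and weaker concern. A download can show a low reading only when a reading was taken, and it cannot show whether another person helped, which is part of the definition of a severe episode. If intervention children test more because STAK-D advises it, more of their episodes will be seen at the same true rate.

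**Working it through.** **Inputs.** The target is 50 dyads (Sample size) with 1:1 allocation (Sequence generation), so 50 / 2 = 25 children per arm. The article gives no expected adverse event rate, share of events attributed to STAK-D or testing frequency by arm. There is therefore no figure of the plan to reproduce, and none is invented here.

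**Step 1: which events can be counted in control.**

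| Event | Primary outcome measures | Harms | Countable in control? |
|---|---|---|---|
| Severe hypoglycaemia | Counted in either group | Listed | Yes |
| Severe hyperglycaemia | Not named; only the general causal definition could cover it | Listed, arm not stated | Undetermined |
| Injury or other incident | Only if it results from STAK-D activity | Only if believed caused by STAK-D | No |

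**Step 2: what this does to the comparison of injuries and incidents.** Let p be the true risk per child and a the share of true events that meet the definition. The expected number counted in an arm is 25 × p × a.

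- Control, as written: a = 0, so 25 × p × 0 = 0 for every value of p.
- Intervention, as written: 25 × p × a, where a depends on the attribution.
- Difference when the true risk is the same in both arms: 25pa − 0 = 25pa. This is above zero whenever p and a are above zero, although STAK-D has no effect.
- With one cause-neutral definition, a is the same in both arms and the difference is 25a × (p in intervention − p in control). This is zero when the risks are equal.

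**Step 3: hypoglycaemic episodes.** Recorded episodes = true episodes × share captured by testing. The recorded ratio between arms is therefore the true ratio × (share captured in intervention / share captured in control). With equal testing the second factor is 1 and nothing is distorted. If intervention children test more, it can exceed 1. The only testing figure in the article is in the exclusion criteria, where fewer than four tests a day is an indicator of poor management. That criterion applies before randomisation and says nothing about a later difference between arms.

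**Step 4: does the existing parent report fill the gap for severe episodes?** Parents in both arms report severe episodes over the past 12 months with the PHFS (Parent measures).

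- At T1 (8 weeks), 52 − 8 = 44 of the 52 weeks lie before baseline: 44 / 52 = 85%.
- At T2 (6 months), 12 − 6 = 6 of the 12 months lie before baseline: 50%.

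The item is asked in both arms and does not depend on cause, but it cannot isolate episodes during the trial.

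**The case against.** **The main safety event is protected.** This stands. Severe hypoglycaemia counts in either arm whatever its cause, so the causal definition favours neither arm for it.

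**Controls may be able to have other events.** In the Harms section the words on causation may qualify only injuries and incidents, which would leave severe hyperglycaemia free of the causal filter. A reader might infer that control can contribute nothing except severe hypoglycaemia. The documents do not settle that, so the zero is claimed only for injuries and other incidents.

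**The download method is the same in both arms.** It follows usual care, the Background describes STAK-D's testing advice as general, and control families receive guideline-based care whose testing advice is not shown. A reader might infer that the hypoglycaemia comparison is biased by construction. It is not: distortion needs testing to differ by arm, which is plausible but not shown. It would bear mainly on non-severe episodes.

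**Parents already report severe episodes and hospital admissions in both arms.** True, and it partly meets the need. But the 12-month recall reaches back before randomisation, and admissions, asked over 6 months, miss injuries treated elsewhere.

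**The comparison is descriptive.** The Statistical methods section plans no safety test, and no progression threshold concerns adverse events. No test is invalidated. A descriptive count beside a control zero fixed by definition still misleads.

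**Event forms belong in the full protocol.** Detailed recording questions do. Here, however, the article itself states both the definition and the comparison, and they do not fit together.

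**Timing of onset.** A reader might also object that onset is shown relative "to the time of the highest bout of physical activity". That concerns a descriptive listing and does not change which events are counted.

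**Conclusion.** The point holds for injuries and other incidents. As written, their control count is 0 of about 25 children by definition, and the contrast with the intervention arm measures attribution rather than excess risk. This follows from the article's wording and needs no assumption about event rates. How large the misleading difference would be cannot be stated, because it depends on a background rate and an attribution share that the article does not give.

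The status of severe hyperglycaemia in control is undetermined, and the Primary outcome measures and Harms sections must be reconciled on it.

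For hypoglycaemia the conclusion is a caution. Downloads cannot show that another person helped, and an excess of mainly non-severe recorded episodes could arise from more testing alone if testing differs by arm.

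This should be fixed, but it does not undermine the feasibility trial as a whole: the main safety event counts in both arms and the analysis is descriptive. It is better fixed soon. The Trial status section says that recruitment is ongoing, and a later analysis plan cannot recover control events that were never recorded.

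**What to change.** In the Primary outcome measures and Harms sections:

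- Use one cause-neutral definition in both arms. Record all injuries and incidents, severe hypoglycaemia and severe hyperglycaemia from randomisation to T2, with the same questions to both arms at T1 and T2.
- Record the judged relation to STAK-D as a separate field, completed after the event has been entered.
- State whether severe hyperglycaemia counts in control, so that the two sections agree.
- Ask parents in both arms about episodes that needed another person's help since the last visit, in addition to the existing 12-month item.
- Report hypoglycaemic episodes by arm with tests per day beside them as context. Tests per day should not serve as a corrective denominator: if STAK-D moves testing to times around activity, the share of low readings can change without any true change in risk.

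The cost is a few extra parent items at visits that already take place, changes of wording, and more unrelated events to record and list.
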